# INTRODUCTION

The World Health Organization (WHO) defines latent Mycobacterium tuberculosis infection (LTBI) as a state of persistent immune response to stimulation by Mycobacterium tuberculosis antigens without evidence of clinical manifestations of active tuberculosis (TB). It is estimated that a quarter of the world population is infected by this bacterium. Despite the absence of symptoms, there is a risk of these patients developing active TB, especially in the first two years after the primary infection worsened in the case of immunosuppression. Activation occurs in 5-10% of cases (LEITE-JÚNIOR, 2017).

Thus, the evaluation of contacts of TB cases is of relevant importance for the screening of LTBI, which requires proper diagnosis and treatment, with the aim of preventing the development of active TB in the future, also interrupting the disease transmission cycle. In Brazil, the National Tuberculosis Control Program/Ministry of Health (PNCT) considers any person who lives in the same environment as the index case as contact at the time of diagnosis of TB. Contacts under the age of five, people with HIV and people with high-risk conditions should be considered a priority in the process of evaluating contacts and treating LTBI (BRASIL, 2017).

The drug Isoniazid is used worldwide for the treatment of LTBI and reduces the risk of illness by 60 to 90%, depending on adherence and duration of treatment (WHO, 2015). As recommended by the Health Surveillance Guide (2017), the current regimen indicated and available for the treatment of LTBI is with the presentation of Isoniazid 100mg in a dosage of 5 to 10 mg/kg/day (maximum dose of 300mg/day) in 270 doses that should be taken from 9 to 12 months (BRASIL, 2017). However, from 2018, Isoniazid 300mg will also be made available to the health network, which should be incorporated by the services. In other words, there will be two presentations of Isoniazid (100mg and 300mg) in the units studied to be used in the treatment of LTBI. Studies carried out by FIOCRUZ indicate that the two formulations have bioequivalence (Daher et al, 2015).

The two presentations of Isoniazid (100mg and 300mg) will be available to be used as needed depending on the weight range of adults and children. Since overdose of Isoniazid can lead to severe drug hepatitis and death, correct use is imperative to ensure that people undergoing treatment for LTBI receive the correct dose of Isoniazid.

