# METHODS

STUDY STEPS

First step

Research sites and Study design

This step will be carried out in Brasília, Curitiba, Santa Catarina, Ribeirão Preto, Espírito Santo in the form of a pragmatic, open-label, randomized clinical trial in health units that provide care to patients with Tuberculosis and whether or not they have a Tuberculosis Control Program (PCT acronym in Portuguese). ). The health facilities that prescribe LTBI treatment will be chosen. From June 2018 to March 2019, people over 18 years of age with indication for LTBI treatment will be invited to participate in this study.

After signing the informed consent term, the contacts will be randomized to receive Isoniazid 100mg or 300mg and will be followed up until the end of treatment.

The primary outcome will be the success rate of LTBI treatment in the new 300mg formulation represented by the proportion of subjects with 270 doses of isoniazid between 9 to 12 months.

Secondary outcomes will be evaluated by comparing adverse effects in the two groups (Isoniazid 100mg or 300mg).

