**Assessment of knowledge, attitudes and practices**

We will establish as "knowledge about LTBI" for this study, the respondent who correctly answers at least five of the ten questions described below:

- Do patients with latent tuberculosis infection (LTBI) also have symptoms of pulmonary tuberculosis? Respondents are expected to respond negatively to this question.

- How would you make the laboratory diagnosis of LTBI? The interviewee is expected to answer: "mainly using the tuberculin skin test" and others such as IGRA mainly in patients vaccinated with BCG, in addition to the x-ray.

- How is the tuberculin skin test performed? The respondent is expected to respond: "(The antigen) is applied (0.1mL) intradermally (in the middle third) on the forearm)"

- How long does it take to get the tuberculin skin test result? Respondent is expected to respond: "(Preferably) within 48 to 72 hours of application"

- Would you answer that adults with a tuberculin skin test with a result above 5mm, but normal x-ray, should undergo treatment for LTBI? The respondent is expected to answer "Yes".

- Should children under 10 years of age, contact with a tuberculosis case, receive treatment for LTBI with a tuberculin skin test result > 10mm if vaccinated less than two years ago? The respondent is expected to answer: "Yes (they are even a priority)"

- Should the treatment for LTBI be the responsibility of the primary care service? Respondent is expected to answer "Yes"

- Is the treatment for LTBI conducted using isoniazid or rifampicin? Respondent is expected to answer "isoniazid"

- What is the maximum amount that a patient undergoing LTBI treatment should receive per day of the indicated drug? The respondent is expected to answer "300 mg/day".

- How long is the treatment for LTBI recommended? The respondent is expected to answer "six to nine months"

- In which situations is LTBI treatment recommended for people living with HIV/AIDS? The interviewee is expected to answer “Normal X-ray and PT >= 5mm, contact of a bacilliferous patient independent of PT and PT < 5mm and with a documentary record of having had PT >= and not undergoing chemoprophylaxis; radiological scar of TB without treatment record.

The 2011 Manual of Recommendations for Tuberculosis Control in Brazil (BRASIL, 20113) was used as the standard text for the preparation of the questions. Attitudes and practices will also be measured in an attached questionnaire.

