**Data analysis:**

The variables will be summarized using measures of frequency, and of central tendency and dispersion, being those that concern knowledge, attitudes and practices in the face of LTBI care. Categorical covariates will be tested using Pearson's chi-square test (or Fischer's Exact test) and continuous ones with Student's T test (or Wilcoxon) will be tested as factors associated with knowledge about LTBI. Variables tested in the bivariate analysis with p value < 0.20 will be taken to the multivariate analysis (logistic regression). In the end, it is expected to assume as factors associated with the lack of knowledge about LTBI those variables that, at the end of the multivariate analysis, present a value of p <0.05. Data will be collected through an electronic questionnaire with pre-coded and open questions, previously tested in a group of subjects similar to those included in the research to confirm the adequacy of the instrument, aiming at the quality of the information obtained.

Textual responses will be coded. The variables will be grouped as follows: adequate or sufficient and insufficient knowledge.

In the outcomes in relation to CAP, the variables will be grouped as follows: adequate or sufficient knowledge regarding the adequacy of the prescription in both doses and inadequate or insufficient knowledge, when knowing the adequacy of only one of the doses. The attitude will be considered adequate when it agrees with the indication of treatment for all the nominees and inappropriate when it does not agree or does not carry out the indication. Regarding the practice of indicating treatment, it will be divided into two groups: those that indicate treatment for LTBI (group 1) and those that do not (group 2).

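### Stage 2 knowledge score: the cut-off refers to ten questions but eleven are listed, and the treatment-duration key does not match the 9 to 12 month regimen the protocol calls current

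*Protocol*

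**What the plan says.** The second stage is a cross-sectional survey of knowledge, attitudes and practices among professionals who prescribe, dispense or monitor LTBI treatment. The planned size is 56 (Protocol, second stage, Participants and sample size).

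- **Cut-off.** Under Assessment of knowledge, attitudes and practices, knowledge about LTBI is credited to "the respondent who correctly answers at least five of the ten questions described below". A bulleted list of questions with expected answers follows.
- **Duration key.** For the recommended length of treatment the expected answer is "six to nine months". The same section says that a 2011 national manual "was used as the standard text for the preparation of the questions".
- **Regimen.** The Introduction, citing a 2017 guide, describes "the current regimen indicated and available for the treatment of LTBI" as isoniazid "in 270 doses that should be taken from 9 to 12 months". The primary outcome in Methods, first step, is the "proportion of subjects with 270 doses of isoniazid between 9 to 12 months".
- **Use of the score.** In the second-stage Data analysis section, covariates "will be tested as factors associated with knowledge about LTBI". Those with p < 0.20 go into a logistic regression. On open answers that section says "Textual responses will be coded" and gives no further rule.

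**The concern.** The protocol itself fixes the cut-off, the item list and the answer key, and they disagree in two places.

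First, the cut-off refers to ten questions while eleven are listed. The rule could mean five correct out of ten, with one unnamed item dropped, or five correct out of all eleven. The second is easier to reach.

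Second, the duration key conflicts with the regimen on which the rest of the protocol is built. The two ranges share only the nine-month point. The respondents work in the units where the trial's regimen is in use, so 9 to 12 months is a plausible answer. It falls outside the key as written, whereas six months falls inside it.

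At stake is a binary outcome in a small sample. Respondents who cross the cut-off because of the item count or the key change both the reported share with knowledge and the outcome variable in the regression.

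**Working it through.** **1. Item count.** The plan's figure is ten. Counting the listed questions: (1) symptoms, (2) laboratory diagnosis, (3) how the skin test is done, (4) time to its result, (5) adults above 5 mm, (6) children under 10, (7) primary care responsibility, (8) isoniazid or rifampicin, (9) maximum daily dose, (10) duration, (11) indications in people with HIV/AIDS. That is eleven. Each has its own question and expected answer, and none is marked as unscored. The cut-off is 5/10 = 50% on one reading and 5/11 = 45.5% on the other.

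**2. Duration.** Key: 6 to 9 months (2011 manual). Introduction: 9 to 12 months, 270 doses (2017 guide). Methods: the same 270 doses in 9 to 12 months. The overlap is nine months only.

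**3. Inputs for size.** The number of respondents is 56, as stated in the protocol (47 × 1.2 = 56.4). The protocol gives no item probabilities, so everything below rests on assumptions: independent items with a common probability p of a correct answer, p = 0.4 to 0.7.

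**4. Effect of the item count.** With X the number correct, an eleventh item changes the class only for a respondent with exactly four correct on the other ten. The shift is therefore P(X = 4 of 10) × q, where q is the chance of getting the extra item right.

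| p | P(X ≥ 5 of 10) | P(X ≥ 5 of 11) | Difference (q = p) | × 56 |
|---|---|---|---|---|
| 0.4 | 0.367 | 0.467 | 0.1003 | 5.6 |
| 0.5 | 0.623 | 0.726 | 0.1025 | 5.7 |
| 0.6 | 0.834 | 0.901 | 0.0669 | 3.7 |
| 0.7 | 0.953 | 0.978 | 0.0257 | 1.4 |

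The last item, on HIV, has a long, multi-part expected answer and may be harder than the rest. For p = 0.4, 0.5, 0.6 and 0.7, P(X = 4 of 10) = 0.2508, 0.2051, 0.1115 and 0.0368. Multiplying by q and by 56:

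- q = 0.2: 2.8, 2.3, 1.2 and 0.4 respondents
- q = 0.1: 1.4, 1.1, 0.6 and 0.2 respondents

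**5. Effect of the duration key.** Let r be the share of all respondents who answer 9 to 12 months and are coded wrong. The key decides the class only for those with exactly four correct on the other scored items, so the number misclassified is 56 × r × P(exactly 4 of the others). With ten items scored there are nine others, and the probabilities are 0.2508, 0.2461, 0.1672 and 0.0735. With eleven scored there are ten others, with the probabilities in step 4.

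| r | Ten scored: p = 0.4 / 0.5 / 0.6 / 0.7 | Eleven scored: p = 0.4 / 0.5 / 0.6 / 0.7 |
|---|---|---|
| 10% | 1.4 / 1.4 / 0.9 / 0.4 | 1.4 / 1.1 / 0.6 / 0.2 |
| 25% | 3.5 / 3.4 / 2.3 / 1.0 | 3.5 / 2.9 / 1.6 / 0.5 |
| 50% | 7.0 / 6.9 / 4.7 / 2.1 | 7.0 / 5.7 / 3.1 / 1.0 |

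**The case against.** The best defence has five parts.

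- **The count may be a slip.** The cut-off is an absolute five, applied to the questions listed, and no exclusion is stated. The natural reading is then five of eleven, and the appended questionnaire, which is not available here, may settle it. This is fair, but the text still gives two numbers.
- **The ranges overlap.** At one dose a day, 270 doses take nine months, so 9 to 12 months can be read as a completion window. A nine-month answer satisfies both. The mismatch is indeed partial and concerns one item. It remains true that the protocol's own regimen, stated in full, does not match the key.
- **Coding detail and pre-testing.** Coding of open answers is commonly left to a later document, and the questionnaire is to be pre-tested. Either could catch the problem, but neither corrects a key that the protocol itself fixes. The plasma substudy section also places the end of treatment at the sixth month. That is a further inconsistency within the protocol and does not reconcile the key with the Introduction.
- **The upper figures are soft.** The 7.0 of 56 needs low overall scores, half of respondents giving the 9 to 12 month answer, and independence between items. Respondents who know the current regimen probably know more of the other answers, which would lower the figure. This stands.
- **The class serves no listed objective directly.** The survey objectives concern compliance in prescribing and dispensing, for which Data analysis uses a separate rule based on knowing both doses. This also stands and limits the importance of the point.

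**Conclusion.** Both inconsistencies are in the text and the concern holds, as a minor point. The knowledge class cannot be scored unambiguously as written, and its duration key fails to credit the regimen that the protocol calls current. Confidence is high for the count and the mismatch. The number of respondents affected is only illustrative, because it depends on assumed item probabilities and independence: from a fraction of one respondent to about six of 56 for the item count, and up to seven for the key under the most unfavourable assumptions. If respondents score well (p = 0.7), the figures fall to 1.4 or fewer and 2.1 or fewer. The reach stops at this one survey outcome and its factor analysis. The randomised comparison, the survey sample size and the both-doses knowledge outcomes are not affected.

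**What to change.** In Assessment of knowledge, attitudes and practices:

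1. State how many items are scored. Either name the unscored question, or say that the cut-off of five applies to all eleven.
2. Re-key the duration item so that 9 to 12 months or 270 doses counts as correct, and say whether a six-month answer still does.

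The cost is one sentence and one answer-key entry. If the survey has already been run, re-score from the stored item answers; no new data are needed.

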**Data analysis:**

The variables will be summarized using measures of frequency, and of central tendency and dispersion, being those that concern knowledge, attitudes and practices in the face of LTBI care. Categorical covariates will be tested using Pearson's chi-square test (or Fischer's Exact test) and continuous ones with Student's T test (or Wilcoxon) will be tested as factors associated with knowledge about LTBI. Variables tested in the bivariate analysis with p value < 0.20 will be taken to the multivariate analysis (logistic regression). In the end, it is expected to assume as factors associated with the lack of knowledge about LTBI those variables that, at the end of the multivariate analysis, present a value of p <0.05. Data will be collected through an electronic questionnaire with pre-coded and open questions, previously tested in a group of subjects similar to those included in the research to confirm the adequacy of the instrument, aiming at the quality of the information obtained.

Textual responses will be coded. The variables will be grouped as follows: adequate or sufficient and insufficient knowledge.

In the outcomes in relation to CAP, the variables will be grouped as follows: adequate or sufficient knowledge regarding the adequacy of the prescription in both doses and inadequate or insufficient knowledge, when knowing the adequacy of only one of the doses. The attitude will be considered adequate when it agrees with the indication of treatment for all the nominees and inappropriate when it does not agree or does not carry out the indication. Regarding the practice of indicating treatment, it will be divided into two groups: those that indicate treatment for LTBI (group 1) and those that do not (group 2).

Similarly, professionals who participate in the dispensing process at baseline will be evaluated. The variables will be grouped as follows: adequate or sufficient knowledge, when the professional is able to identify the use of Isoniazid 100mg and use of Isonizaide 300mg and inadequate or insufficient, when knowing the indication for the use of only one of the doses. The attitude will be considered appropriate when in possession of the prescription, the professional checks the presentation of Isoniazid and inappropriate when not checking before dispensing the drug. Regarding the practice, it will be divided into two groups: those who keep the two presentations in different places (group 1) and those who keep the two presentations in the same place (group 2).

[figure not shown]

[figure not shown]

[figure not shown]

[figure not shown]

[figure not shown]

[figure not shown]

[figure not shown]

[figure not shown]

[figure not shown]

Figure 3- timeline for selecting the study sample

Third Stage

It will be a qualitative research that, according to Denzin and Lincoln (2006), involves an interpretive approach to the world, which means that its researchers study things in their natural settings, trying to understand phenomena in terms of the meanings that people give to them. The theoretical axis adopted will be that of social representations, understood as modalities of practical knowledge, oriented towards communication and understanding of the social, material and ideational context in which we live.

The contents expressed by the individual are essentially heterogeneous; they translate the thinking, the common sense of a given social group, understanding the individual in a social perspective, because reality is socially constructed (SPINK, 2004). For Marx (1994) the human essence is not something abstract and immanent to each individual. It is, a reality, built in the set of social relationships that can be reported, can be observed; the speeches and experiences of social actors provide relevant data for the researcher, through meetings and conversations, to expand access to the production of meaning and the representations of individuals constructed (SPINK, 2004).

As a method, the collective subject discourse (CSD) will be used, a methodological strategy in qualitative research for the construction of the CSD, which consists of a qualitative way of representing the thinking of a collectivity, aggregating, in a synthesis discourse, the discursive contents of similar meaning issued by different people. Thus, each individual interviewed in the study, chosen based on criteria of social representativeness, contributes with his share of a fragment of thought for collective thinking (LEFÈVRE and LEFÈVRE, 2004). This methodological procedure implies a definition, based on an empirical perspective, that the collective character of social thought is the amount of choices made by a certain set of individuals belonging to a certain community; although expressed individually, it is socially shared, translating the nature of collective thinking (LEFÈVRE and LEFÈVRE, 2004).

Based on the theory of social representation, the CSD is a method of presenting qualitative research results that includes testimonies as raw material in the form of one or several synthesis discourses, written in the first person singular, an expedient that aims to express the thought of a collectivity, as if this collectivity were the issuer of a discourse (LEFRÈVE, CRESTANA and CORNETTA, 2003). It is the sharing of ideas and positions. A collective mirror; the speech of a social group.

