Thus, the triad for the correct use of a medication composed of: prescription, dispensing and ingestion needs to be monitored and questions related to the professionals who carry out the prescription, to those who participate in the dispensing process, which differs in each service, and also, questions related to drug intake by the patient bring together a new configuration in Tuberculosis programs and will therefore be the object of this study, as described in Figure 1.
[figure not shown]

Figure 1 - Processes related to the triad of evaluation of new dosage

Thus, with the development of the present study, it is intended to understand the process of implementation of the presentation of Isoniazid 300mg for the treatment of LTBI in some health units in different regions of the country in order to identify potential risks in the process of using the drug. medication and ensure patient safety.

To carry out this study, three steps will be adopted that may occur simultaneously. The first stage will be a pragmatic clinical trial with patients LTBI diagnosed in health facilities in Brasília, Curitiba, Florianópolis, Ribeirão Preto - SP and Vitória, which will evaluate the prescription, dispensing and ingestion of the two dosages provided by the PNCT. The second stage will be a cross-sectional study using the 'Knowledge, attitude and practices' methodology to verify compliance in prescribing and dispensing. And the third stage will be a qualitative study with health professionals to analyze the speeches of professionals who prescribe the drug and professionals who dispense the new dosage of 300mg. In this sense, the evaluation of this new presentation will consist of stages that complement each other, as shown in Figure 2:

[figure not shown]

Figure 2. Steps for the Evaluation of Implementation of Isoniazid 300mg for the treatment of LTBI

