**Participants and sample size**

All those involved will be invited to participate in prescribing, dispensing and monitoring LTBI treatment in primary care health units and reference units included in stage 1 in Brasília, Curitiba, Florianópolis, Ribeirão Preto and Vitória.

For the sample calculation, the STATA 15.0** program was used. A 70% hit ratio was considered, a power of 80% to detect differences and a significance level of 5%. Thus, it is estimated that 47 subjects are needed. As this is a cross-sectional study, the study design effect of 1.2 was applied. Therefore, 56 subjects will be needed.

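### The stage 2 survey is enlarged by a design effect of 1.2, but its named tests treat colleagues in one health unit as independent, and tablet storage is counted per professional rather than per unit

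*Protocol*

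**What the plan says.** In the Protocol, Second stage, Participants and sample size, everyone involved with LTBI treatment in the stage 1 primary care and reference units of five cities is invited. The size rests on "A 70% hit ratio was considered, a power of 80% to detect differences and a significance level of 5"%, which gives 47. The next step is "As this is a cross-sectional study, the study design effect of 1.2 was applied", which gives 56. No other reason for the 1.2 appears.

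Under Data analysis in the same stage, factors possibly linked to LTBI knowledge are examined as follows: "Categorical covariates will be tested using Pearson's chi-square test (or Fischer's Exact test) and continuous ones with Student's T test (or Wilcoxon". Variables with p below 0.20 go into a logistic regression, and those with p below 0.05 are declared associated. No term, variance correction or stratification for health unit or city is named, and no confidence interval is specified for this stage.

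The same section divides dispensing professionals, on practice, into "those who keep the two presentations in different places (group 1) and those who keep the two presentations in the same place (group 2"). No test is attached to this item and no count per unit is planned. The Introduction speaks of "those who participate in the dispensing process, which differs in each service".

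**The concern.** A design effect allows for respondents who carry less information than the same number of independent ones. Sizing with 1.2 and then testing as if it were 1.0 puts two different variance assumptions into one plan. A cross-sectional design does not by itself create a design effect. Nesting of staff in units would, but the protocol does not give that as the reason.

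Two results are at stake. First, a factor that differs mainly between units or cities could be declared associated with LTBI knowledge somewhat too often. Second, the storage item bears on the protocol's aim of finding risks in how the two strengths are used. Where several colleagues describe one pharmacy, the proportion repeats that arrangement and weights each unit by how many of its staff answered. The result is not the share of units that keep the strengths apart.

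**Working it through.** **Inputs.** From Participants and sample size: expected proportion 70%, power 80%, significance level 5%, design effect (D) 1.2, sizes 47 and 56. From Data analysis: screen at 0.20, decision at 0.05. The protocol does not give the comparator proportion, the sidedness, the number of respondents per unit (m) or the within-unit correlation (ICC).

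**1. The plan's own figures.** A one-sample test of 70% against an assumed 50%, two-sided:

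n = [(1.96·√0.25 + 0.8416·√0.21) / 0.20]² = 46.63, so 47.

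46.63 × 1.2 = 55.95, so 56. (47 × 1.2 = 56.4; the difference is only rounding.) Both stated sizes reproduce, so the sample size is not at fault.

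**2. What 1.2 would imply for the tests.** If the variance is really D times what the test assumes, the true level is 2·[1 − Φ(z/√D)], with √1.2 = 1.095:

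- decision at 5%: 1.96/1.095 = 1.789, true level 7.4%
- screen at 20%: 1.2816/1.095 = 1.170, true level 24.2%

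The effective sample is 56/1.2 = 46.7.

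**3. Which tests this applies to.** The formula in step 2 suits a factor that is constant within a unit. With D = 1 + (m − 1)·ICC, a chi-square test on 56 respondents with a 70% outcome was simulated (beta-binomial, 40,000 runs per setting). The values of m and ICC are assumptions.

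| m | ICC | D | Factor constant within unit: true level at 5% / 20% | Factor balanced (or nearly) within units: true level at 5% / 20% |
| --- | --- | --- | --- | --- |
| 4 | 0.067 | 1.2 | 7.6% / 25.0% | 4.6% / 19.2% |
| 7 | 0.033 | 1.2 | 7.5% / 24.8% | 4.3% / 18.8% |
| 4 | 0.2 | 1.6 | 12.4% / 32.4% | 3.2% / 16.1% |
| 7 | 0.2 | 2.2 | 19.5% / 41.0% | 2.9% / 15.4% |

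The error therefore runs in both directions: too liberal for factors that vary between units, slightly too strict for factors balanced within them.

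**4. Storage.** If colleagues in a unit all report the same arrangement (ICC = 1), then D = m. Even if all 56 answered, they would carry the information of 56/m arrangements: 28, 14 or 7 for an assumed 2, 4 or 8 respondents per unit. Only dispensing staff are classified, so the true base is smaller. To show the weighting, take two units, one with 8 respondents that stores the strengths together and one with 2 that stores them apart. The staff-weighted proportion stored apart is 2/10 = 20%; the proportion of units is 1/2 = 50%.

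**The case against.** The strongest reply is that the mismatch depends on an inference. The protocol ties the 1.2 to the cross-sectional design and never to grouping in units. That stands, and it is why every figure at 1.2 is conditional. It does not clear the plan, because the stated reason does not explain the number and the nesting follows from how staff are invited.

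A reader might infer that all stage 2 p-values and intervals are too optimistic. The protocol does not support that. It names no interval for this stage; the relative risk with its 95% interval belongs to the stage 1 trial. Most covariates listed under Data collect are personal (sex, age, education, profession, training received), and for factors that vary within units the test can be slightly conservative. The liberal error concerns factors that differ mainly between units or cities.

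A reader might also infer large false-positive rates or much too narrow intervals for storage. These would describe an analysis that is not planned, since the protocol gives no test and no interval for that item, and they would rest on an assumed number of respondents per unit. That storage belongs to the unit is itself an inference: the Introduction says the dispensing process differs by service but does not mention storage, and the questionnaire is not shown. What remains is repeated counting in a descriptive proportion.

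Finally, a variance estimator is often left to a statistical analysis plan, and logistic regression is compatible with a clustered one. That is fair for the model. It is weaker for the bivariate tests, which the protocol fixes by name and which also decide what enters the model.

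**Conclusion.** The point holds in a limited form. Respondents are nested in health units, the sample is inflated by 1.2 without an adequate reason, and the named tests make no allowance for unit. If the 1.2 reflects within-unit correlation, a nominal 5% test of a between-unit factor has a true level of about 7.4%, and the 20% screen about 24.2%; tests of factors balanced within units run at about 4.3% to 4.6%. Larger distortions (12.4% to 19.5%) need an assumed ICC of 0.2. The effect is modest, belongs to the secondary survey and does not touch the randomized comparison.

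The storage proportion is better reported per unit. This assumes that colleagues share one arrangement, which is likely but not stated. The comparator of 50% and the two-sided test are inferred because they reproduce 47.

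**What to change.** In the second stage of the protocol:

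- **Participants and sample size:** state why 1.2 was used. If the reason is clustering, give the assumed respondents per unit and ICC.
- **Data analysis, knowledge factors:** state that the bivariate tests and the logistic regression account for health unit, for example by a random intercept or cluster-robust variance by unit. Add a small-sample correction, because with 56 respondents the units may be few and uncorrected robust errors are then too small. Survey-sampling commands are a poor fit, because units are chosen by treatment volume and not drawn at random.
- **Data analysis, storage:** record storage once per health unit and report the proportion of units keeping the two strengths apart. Keep the professional as the unit for knowledge and attitude.

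This needs some wording and a unit identifier on each questionnaire, if there is not one already, and no extra respondents. The price is somewhat wider uncertainty and a smaller denominator for storage.
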